### Objectives {7}

The first objective of the current study is to evaluate the effectiveness of patient-tailored PROfeel lifestyle advices and generic dietary advices as interventions on “fatigue severity”, “quality of life”, and “self-efficacy” on the group level. The second objective is to explore the same, but on the individual level for all participants (i.e., multiple *N*=1). If patient-tailored PROfeel lifestyle advices are effective, the third objective is to investigate through which mechanisms the effects have been reached, by exploring changes in the dynamic ESM networks pre-post intervention. The fourth objective is to explore the biological profile (e.g., immunological profile, HPA axis, mitochondrial dysfunction, and gut microbiome) of adolescents and young adults with QFS at baseline. Participants with QFS will be compared to participants with CFS/ME and JIA, as well as healthy controls. The fifth objective is to explore relationships between individual improvement differences in “fatigue severity” and subsequent changes in biological profile.

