#### Additional criteria for participants with QFS

All 20 participants must enter the screening process with a (suspected) diagnosis of QFS according to the Dutch guidelines [25]. Participants must have suffered from debilitating fatigue with detrimental effects on daily functioning in work and/or private life for at least 6 months. The debilitating fatigue must have started before the age of 18, and after infection with *Coxiella burnetii*—where fatigue severity increased significantly after infection. All participants in the QFS group must be seropositive for *Coxiella burnetii* and cannot have a diagnosis of chronic Q-fever or recent diagnostics (< 3 months) demonstrating an IgG phase 1 titer of <1:1024 (or 1:512 in case of patients who are immunocompromised, or with a vascular prosthesis or a heart defect). At the time of screening, fatigue must be severe. This is indicated by a score higher than 39 on the Checklist Individual Strength-8 (CIS-8) questionnaire, which ranges from 0 to 56, with higher scores indicating more fatigue [26].

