### Sample size {14}

As described earlier, the QFS-study concerns a RCT with implemented *N*=1 design. The objectives of the study with *N*=1 design do not require a sample size calculation. Therefore, power analysis was performed for the group-level analyses on the primary outcome “fatigue severity”, which will be measured pre-post interventions. Based on previous CBT studies aiming to reduce chronic fatigue [18, 26], with an alpha of .05, power of .80, repeated measures correlation of .23, and an anticipated Cohen’s *f* effect size of .5, the sample size calculation for repeated measures 2 × 2 ANOVA yields *n*=16 per group. Taking into consideration an expected drop-out rate of 20% from previous single-subject experimental case research with multiple measurement on severe fatigue in adolescent patients with an immune dysregulation disorder, we will include 20 participants per group (i.e., QFS, CFS/ME, JIA), resulting in *N*=60. With *N*=60, it was decided upon expert medical and research lab opinion to include up to 80 healthy controls to increase the likelihood of recruiting healthy controls with seropositive *Coxiella burnetii* status, of observing contrasts in biological parameters, and to enable matching for age and gender as much as possible.

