## Data collection and management

### Plans for assessment and collection of outcomes {18a}

The primary outcome of the intervention study is “fatigue severity” as measured by the subscale “fatigue severity” (8 items) of the Checklist Individual Strength-20 (CIS-20). The subscale consists of 8 items (CIS-8). Participants will receive the CIS-8 once a week throughout the study as a survey in the Ethica smartphone app. The weekly CIS-8 has a scoring range of 8–56, with higher scores indicating more fatigue. The CIS-8 has good reliability and discriminative validity [35]. A reduction of 1 standard deviation (SD) is considered clinically relevant.

Secondary outcomes of the intervention study are “quality of life” and “self-efficacy”. Per construct, one VAS item will be added to the weekly CIS-8 questionnaire. In addition, these outcomes will be measured with questionnaires in KLIK, a web-based survey portal (www.hetklikt.nu). “Quality of life” will be measured with the Pediatric Quality of Life Inventory 4.0 Generic Score (PedsQL GCS). This questionnaire consists of four subscales (i.e., physical, emotional, social, and school or work functioning), with total- and subscores ranging from 0 to 100. Higher scores indicate a higher quality of life. The PedsQL GCS has good validity and reliability [36]. An increase of 1 SD is considered clinically relevant. “Self-efficacy” is defined as a sense of control over fatigue symptoms and will be measured with the Self-Efficacy Scale-28 (SES-28). This questionnaire consists of 5 items that inquire about the sense of control related to fatigue, with higher scores indicating more sense of control [37]. An increase of 1 SD will be considered clinically relevant.

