## Statistical methods

### Statistical methods for primary and secondary outcomes {20a}

To evaluate on the group level the effectiveness of the patient-tailored PROfeel lifestyle advices against generic dietary advices in reducing “fatigue severity” and improving “quality of life” and “self-efficacy” (objective 1), two statistical tests will be performed. The first test, is a 2 × 2 ANCOVA with “fatigue severity” at T2 as dependent variable, “fatigue severity” at baseline as covariate, and intervention condition as fixed factor. This test is used to compare the reduction in “fatigue severity” for the PROfeel-first group against the dietary-first group. The second test is a repeated measures 2 × 2 ANOVA to test whether the order in which participants received the advices is of relevance. The same tests will be performed for secondary outcomes “quality of life” and “self-efficacy”.

To evaluate the effectiveness of the patient-tailored PROfeel lifestyle advices and generic dietary advices in reducing “fatigue severity” and improving “quality of life” and “self-efficacy” at the individual level (objective 2), the permutation distancing test (PDT) will be used. This test is currently under development (see supplement of 41). This test takes into account autocorrelation, handles missing data by making optimal use of all observations, and is specifically developed for *N*=1 designs with a fixed intervention start.

To explore individual effects on pre-post intervention change in the dynamic networks for the participants who first receive patient-tailored PROfeel lifestyle advices first (objective 3), single-subject residual dynamic structural equation modelling (RDSEM) [40] will be used in Mplus. We will model the pre- and post-intervention dynamic networks in one SEM model [41]. This allows for statistical testing of the differences between the pre- and post-network estimates.

To explore the biological profile of adolescents and young adults with QFS and compare it with participants with CFS/ME and JIA, as well as healthy controls (objective 4), we will use between-group ANOVAs and/or linear regression analyses.

Exploration of the relationship between individual differences in “fatigue severity” improvement and biological profile changes pre-post interventions (objective 5) will be conducted with growth mixture modelling (GMM) [42] in Mplus.

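### Objective 2 calls each person's before-after change the effectiveness of each advice, but with a fixed start, entry on high fatigue and no untreated arm that change cannot be separated from time

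*Protocol article*

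**What the plan says.** - **Aim.** The Objectives section says that objective 1 will "evaluate the effectiveness of patient-tailored PROfeel lifestyle advices and generic dietary advices as interventions" at the group level. Objective 2 explores the same for each participant. The statistical methods section repeats the causal wording for the individual level: "To evaluate the effectiveness of the patient-tailored PROfeel lifestyle advices and generic dietary advices in reducing" fatigue severity, with quality of life and self-efficacy alongside.
- **Method.** The permutation distancing test (PDT) is the only method named for objective 2. It is described as made for N=1 "designs with a fixed intervention start". Of its properties the article says: "This test takes into account autocorrelation, handles missing data by making optimal use of all observations". It adds: "This test is currently under development", and refers to a supplement that is not shown.
- **Entry.** For QFS, "At the time of screening, fatigue must be severe", meaning CIS-8 above 39. CFS/ME has the same cut-off and JIA uses above 34.
- **Timeline (Table 1).** Screening is in week 0, an untreated measurement phase runs in weeks 1-4, and the first advice covers weeks 5-16. A second measurement phase runs in weeks 17-20 and the other advice in weeks 21-32. The weekly fatigue score continues throughout.
- **Arms.** Sequence generation describes 1:1 randomisation to which advice comes first. There is no untreated or waiting arm.
- **Weight given to the N=1 part.** Trial design labels it exploratory. The Discussion, however, doubts whether the RCT measures the advices themselves or participants' ability to change behaviour, and then presents the N=1 design as a strength on exactly that issue.
- **Objective 3** goes ahead only if PROfeel proves effective. The article does not say which analysis decides this.

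**The concern.** When the start is the same for everyone and not randomised within the person, the before-after difference is the advice effect plus everything else that changes over those weeks. Two such changes are plausible here: decline in fatigue that would have happened anyway, and regression to the mean after selection on a high score. Allowing for autocorrelation widens the reference distribution but does not remove a drift. Randomising the order helps comparisons between people, not one person's own contrast.

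Participants could therefore be listed as individuals in whom PROfeel, or diet, was effective when neither did anything. The Discussion leans on this analysis to judge the advices, and the gate to objective 3 could be opened by it.

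**Working it through.** The article gives no figure for the individual-level analysis, and the sample size section says none is needed, so there is nothing to reproduce. The size of the problem has to be illustrated.

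**Inputs from the article:** selection in week 0; lead-in in weeks 1-4; first advice in weeks 5-16; second measurement phase in weeks 17-20; second advice in weeks 21-32; a "repeated measures correlation of .23" from the sample size section, whose lag is not stated.

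**Assumptions:** no treatment effect; weekly scores normal with SD 1; entry if the week-0 score exceeds a threshold c, in SD units around the mean of those screened; the PDT compares weeks 1-4 with weeks 5-16. The article gives neither c, nor the shape of the correlation, nor the phases compared.

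**Step 1, mean score at entry.** m(c) = density(c) / upper tail(c). This is 0.288 for c = -1, 0.798 for c = 0 and 1.525 for c = +1.

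**Step 2, equal correlation at every lag.** The expected score in any later week is 0.23 × m(c). Lead-in and intervention means are equal, so the mean drop is 0. The lead-in has absorbed all regression to the mean.

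**Step 3, steadily decaying correlation, AR(1), reaching .23 at 16 weeks.** phi = .23^(1/16) = 0.912. The mean of phi^k is 0.799 over weeks 1-4 and 0.401 over weeks 5-16, a difference of 0.398. For the second advice (weeks 17-20 against 21-32) the difference is 0.184 - 0.092 = 0.092. The mean drop is m(c) times the difference:

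| Threshold c | First advice | Second advice |
|---|---|---|
| -1 SD | 0.288 × 0.398 = 0.11 | 0.288 × 0.092 = 0.03 |
| 0 | 0.798 × 0.398 = 0.32 | 0.798 × 0.092 = 0.07 |
| +1 SD | 1.525 × 0.398 = 0.61 | 1.525 × 0.092 = 0.14 |

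**Step 4, a mixture.** Take a stable personal level with variance share .22, weekly noise .20 and an AR(1) part of .58 with phi .7. The 16-week correlation is again about .22, and the first-advice drop is 0.07, 0.18 and 0.35 SD for the three thresholds.

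**Step 5, effect on a test.** As a stand-in for the PDT, a generic two-sided phase-permutation test at 5% was simulated on weekly scores with independent residuals, no advice effect and an assumed decline in within-person SD.

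| Assumed decline | First advice declared effective | Second advice |
|---|---|---|
| None | about 5% | about 4% |
| Linear, 0.5 SD per 12 weeks | about 8% | about 9% |
| Linear, 1 SD per 12 weeks | about 19% | about 18% |
| Linear, 2 SD per 12 weeks | about 49% | about 47% |
| Front-loaded, 2 SD in total, half-life 4 weeks | about 28% | about 6% |

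Selection-driven or front-loaded decline therefore favours the first advice, while a steady decline credits both about equally.

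**The case against.** The strongest reply has four parts.

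1. *The baseline is not the screening score.* Four untreated weeks follow selection, and step 2 shows that they can remove all regression to the mean. QFS fatigue must also have lasted at least 6 months, so fast spontaneous recovery is not a given. This stands. The documents support saying that decline can be counted as response, not that it will be.
2. *The PDT may deal with trend.* Its supplement is not shown, and a condensed article's silence does not prove that trend is ignored. This stands as a caution. Still, any trend adjustment would have to project a 4-week lead-in over the 12 weeks of advice, and that is itself an assumption.
3. *The randomised comparison is already there.* The T2 ANCOVA compares PROfeel-first with diet-first, and both arms share selection, lead-in and calendar. This stands, and objective 1's test needs no change.
4. *The N=1 part is exploratory.* This limits the weight of the point, but it does not make effectiveness the right word for an uncontrolled change, particularly given the Discussion's reliance on it.

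A reader might also go further and infer a false-responder rate from the statement "A reduction of 1 standard deviation (SD) is considered clinically relevant". The documents do not make that 1-SD mark the decision rule of the PDT or of objective 2. Under equal correlation, a fall of at least 1 SD between two visits has probability P(Z > 1/√(2 × 0.77)) = P(Z > 0.81) = 21%. A rise of at least 1 SD is just as likely, so this is symmetric noise and not natural decline. Nor do the documents support the inference that only the first advice gains: step 5 shows that this depends on the shape of the decline.

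**Conclusion.** The point holds in a limited form. As planned, a person's PDT result shows change across a phase boundary and cannot by itself show that the advice caused it, so labelling it effectiveness of each advice is not supported by the design. In group-mean terms, with no treatment effect, the spurious fall around the first advice is between 0 and about 0.6 SD. Where it lies in that range depends on the correlation structure and the entry threshold, neither of which the article gives. The test simulation rests on assumed declines and a generic stand-in, so it shows direction rather than the PDT's own error rate. The randomised T2 ANCOVA is untouched. It would be too strong to say that the trial's main comparison is biased, or that the individual analyses have no use.

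**What to change.** In the statistical methods section, objective 2:

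- Keep the individual PDT results, but describe them as within-person change, not as effectiveness. Align the Discussion's remark on the N=1 design with this.
- For period I, add one table by randomised arm: PDT effect sizes and the proportion of individuals with a PDT-detected improvement, with the between-arm difference and its confidence interval.
- Base any statement that PROfeel works better than dietary advice on that difference together with the T2 ANCOVA.
- In the Objectives section, state that objective 3's condition refers to the randomised contrast.

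The cost is wording and one table from data already to be collected. The downside is that the trial would not claim from N=1 data that each advice is effective on its own, and equal benefit from both advices would not show in the between-arm contrast.

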### Intervention description {11a}

#### Patient-tailored PROfeel lifestyle advice

The RCT starts with a 4-week ESM assessment (see Table 1 for timeline). ESM is an innovative, validated, structured diary technique for longitudinal measurements of fluctuating states, that captures life as it is lived on the spot [22, 23, 29]. Multiple ESM applications are available for smartphones. In this study, we use the Ethica application (www.ethicadata.com) in which participants complete ESM surveys (i.e., diaries) approximately 5 times per day. In a first step, ESM data are used by a statistician to compute an individual descriptive report and an individual dynamic report with fatigue-perpetuating dynamic networks, identifying the contemporaneous and time-lag relations between fluctuations in fatigue and behavior, sleep, social context, cognitions, and feelings [23]. In a next step, the investigator uses the descriptive and dynamic reports to produce a reduced PROfeel report. Face-to-face, the investigator and participant discuss the PROfeel report and use shared decision-making to formulate a patient-tailored lifestyle advice. The term “lifestyle” here refers to an area of daily life that can be modified to potentially reduce fatigue and/or improve quality of life and self-efficacy. The combination of ESM with personalized feedback, leading to patient-tailored lifestyle advices, is named PROfeel. Details follow in the sections underneath.

**Table 1 Tab1:** Participant timeline in QFS-study

Week	Activity	Description
0	Screening	Evaluation of participant’s eligibility for the QFS-study by social pediatrician (and pediatric immunologist/rheumatologist in case of JIA diagnosis).
1	Study visit T0	Participant completes baseline KLIK questionnaires and installs the PROfeel app on smartphone to start ESM measurement. Participant also starts weekly measurement (of fatigue, quality of life, and self-efficacy) on smartphone which lasts throughout the study.
1-4	ESM phase I	Participant starts 4 weeks of ESM, with 5 surveys to answer per day. Surveys contain items inquiring after, e.g., fatigue and other symptoms, (social) activities, and affect in the last 3 h.
5	Study visit T1	Participant completes T1 KLIK questionnaires and is randomly allocated to either 12 weeks of patient-tailored PROfeel lifestyle advice or generic dietary advice. Biological samples (i.e., blood, stool, saliva, and hair) are collected for the first time.

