5-16	Intervention I	Participant adheres to allocated advice for 12 weeks. To improve adherence, participant receives a boost from the investigator by phone and/or mail.
17	Study visit T2	Participant completes T2 KLIK questionnaires and evaluates first intervention with investigator. Biological samples (i.e., blood, stool, saliva, and hair) are collected for the second time.
17-20	ESM phase II	Participant starts a second period of 4 ESM weeks, with 5 surveys to answer per day. Survey items are identical to ESM phase I.
21	Study visit T3	Participant completes T3 KLIK questionnaires and is allocated to the other intervention arm (either 12 weeks of patient-tailored PROfeel lifestyle advice or generic dietary advice).
21-32	Intervention II	Participant adheres to allocated advice for 12 weeks. To improve adherence, participant receives a boost from the investigator by phone and/or mail.
33	Study visit T4	Participant completes T4 KLIK questionnaires and evaluates second intervention with investigator. If fatigue remains severe, participant can be referred to ECCF for post-trial care. Biological samples (i.e., blood, stool, saliva, and hair) are collected for the third time.
33-60	Follow-up	Weekly measurement (of fatigue, quality of life, and self-efficacy) on smartphone continues until 12 weeks after T4. During week 60, participant completes follow-up KLIK questionnaires, marking the end of QFS-study participation.

Healthy controls only have one study visit during which questionnaires (i.e., baseline KLIK, Eetscore, and optionally Food Frequency Questionnaire) and biological samples (i.e., blood, stool, saliva, and hair) are collected

*ESM* experience **s**ampling methodology, *CIS-8* Checklist Individual Strength-8 questionnaire, *ECCF* Dutch Expert Centre for Chronic Fatigue

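### Objective 3 asks about PROfeel's mechanism but analyses network change in the PROfeel-first arm only, leaving a randomised comparator with the same two ESM phases unused

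*Protocol article*

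**What the plan says.** Objectives {7} makes the third objective conditional on PROfeel being effective and then sets out to "investigate through which mechanisms the effects have been reached" by exploring how the dynamic ESM networks change from before to after the intervention.

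Statistical methods {20a} plans single-subject residual dynamic structural equation models (RDSEM) "for the participants who first receive patient-tailored PROfeel lifestyle advices first (objective 3". The pre- and post-intervention networks go into one model, and the stated benefit is: "This allows for statistical testing of the differences between the pre- and post-network estimates". No comparison between arms is named for this objective, and the section on additional analyses {20b} states that there will be none.

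Table 1 gives the data collection without distinction by arm. In weeks 1-4, before allocation at T1: "Participant starts 4 weeks of ESM, with 5 surveys to answer per day". In weeks 17-20, after the first 12-week advice: "Participant starts a second period of 4 ESM weeks, with 5 surveys to answer per day. Survey items are identical to ESM phase I". The switch comes only in week 21: "Participant completes T3 KLIK questionnaires and is allocated to the other intervention arm".

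**The concern.** Asking which mechanism produced an effect is a causal question. A pre-post comparison within treated participants shows that a network changed. It does not show that PROfeel changed it. Roughly four months separate the two ESM phases, and over that time networks could shift with the passage of time, with the natural course of the fatigue, or because participants have already monitored themselves several times a day for four weeks.

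The trial collects the data that would show such background change, because the randomised dietary-first arm is followed through the same two phases over the same weeks. If that arm is left out, a shift common to both arms could be reported as the way PROfeel works.

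**Working it through.** No figure in the protocol is in dispute. The check consists of setting the sections side by side, counting participants, and one illustration.

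**1. Who has which ESM data (Table 1)**

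| Weeks | PROfeel-first | Dietary-first |
|---|---|---|
| 1-4 | ESM phase I | ESM phase I |
| 5-16 | PROfeel advice | Dietary advice |
| 17-20 | ESM phase II, identical items | ESM phase II, identical items |
| 21-32 | Dietary advice | PROfeel advice |
| 33 onwards | No further ESM phase | No further ESM phase |

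Two things follow. Only PROfeel-first participants have ESM both before and after PROfeel, so they are the only treated cases. Dietary-first participants have ESM over the same interval before they receive PROfeel, so they can serve as controls for that interval.

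**2. How many participants are left out**

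Inputs: N = 60 and 20% drop-out (Sample size {14}); 1:1 allocation stratified by diagnosis group (Sequence generation {16a}).

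- Per arm: 60 / 2 = 30.
- After drop-out, assumed equal in both arms: 30 × (1 − 0.20) = 24.

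The plan uses about 30 (24) participants for objective 3. With the comparator it would be about 30 v 30 (24 v 24).

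**3. What background drift could do (illustration only)**

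The protocol gives no size for drift, so these are assumptions: one autoregressive path of about 0.3, a two-sided 5% test, and standard error of the pre-post difference = √(2 × (1 − 0.3²) / n), with n surveys per phase. The protocol asks for at least 100 of 140 surveys.

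- n = 100: √(2 × 0.91 / 100) = 0.135.
- n = 140: √(2 × 0.91 / 140) = 0.114.

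Expected share of participants with a significant pre-post change when PROfeel has no effect on the path:

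| Drift unrelated to PROfeel | 100 surveys per phase | 140 surveys per phase |
|---|---|---|
| 0 | 5% | 5% |
| 0.1 | 12% | 14% |
| 0.2 | 32% | 42% |
| 0.3 | 60% | 75% |

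With no drift the rate is the nominal 5%, so the test handles sampling error as intended. With drift, the excess looks exactly like an effect of PROfeel. Drift common to both arms would appear in the dietary-first arm too.

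**4. How precise the comparison between arms would be**

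For a two-sample t-test with 24 v 24, 80% power and two-sided 5%, the detectable difference is about 0.83 standard deviations of the individual change estimates. The contrast can therefore show large differences only.

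**The case against.** The best defence is that objective 3 is modest. It is exploratory, works at the level of the individual, and is pursued only if PROfeel proves effective, which the between-arm ANCOVA at T2 is meant to establish. The restriction also has a reason: no ESM phase follows the second intervention, so dietary-first participants cannot show change after PROfeel. Both points stand. The first limits the weight of the concern. The second explains who the treated cases are, but not why the other arm is left out as control.

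Three further objections concern the comparison itself. Dietary advice is an active comparator that the protocol expects may reduce fatigue, so a link changed by both advices would show no difference. Surveys are partly personalised and each PROfeel advice may target a different factor, so averaging over people can dilute person-specific change. And precision is low. These stand as well. They rule out a strict requirement that a mechanism be dismissed wherever the arms do not differ, and they confine the comparison to the fixed items. They do not make an uncontrolled pre-post change evidence of mechanism.

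A reader might also infer two stronger criticisms:

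- **Chance findings cannot be recognised in one arm.** This does not follow. Their rate is the known nominal level of the test. Testing many links is a multiplicity matter and does not measure the bias discussed here.
- **Entry on high CIS-8 scores makes the networks regress to the mean.** The eligibility criteria select on the level of fatigue, whereas the networks describe relations between fluctuations. Selection on level does not by itself show that link strengths will regress.

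**Conclusion.** The concern holds in a limited form. The protocol states a mechanism question, restricts the analysis to PROfeel-first participants, and leaves unused a randomised arm with the same two ESM phases. The planned analysis can describe how individual networks changed. It cannot separate PROfeel from time, natural course or repeated self-monitoring.

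The size is about 30 unused comparators, or about 24 if drop-out is 20% in each arm. How much background change there will be cannot be derived from the protocol; the drift table shows only what would follow under its assumptions.

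A reader should not infer that the effectiveness result is affected. Objective 1 rests on its own between-arm comparison. Nor should a null contrast for objective 3 be read as absence of a mechanism, given the active comparator and the low precision.

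**What to change.** In Statistical methods {20a}, for objective 3:

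1. Fit the same single-subject pre-post RDSEM to every participant with both ESM phases, in both arms, and keep the individual results.
2. Compare the individual change estimates for links among the fixed, non-personalised items between PROfeel-first and dietary-first, adjusted for diagnosis group, and report differences with confidence intervals.
3. Attribute change specifically to PROfeel only with support from that contrast. Report all other within-person change, including links with personalised items, as exploratory pre-post change.
4. State that the contrast is against active dietary advice and that, with about 24 v 24 participants, no difference between arms does not rule out a mechanism.

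The cost is extra computing on data already collected. There is no added burden for participants and no change to the primary analysis. The drawback is low precision, which the intervals will show.
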